### Assessments

For patient outcome we will collect data concerning the LOS, admission to and duration of ICU stay, readmission within 30 days and mortality in hospital or within 30 days after discharge for the baseline group and the intervention group. Furthermore we will collect data for possible confounders of patient’s outcome, namely age, sex, community-or hospital acquired infection, Charlson comorbidity index [15,16], use of antibiotics during the previous 30 days, and clinical condition as assessed by the Modified Early Warning System [17]. To calculate QI performance we will collect data concerning the number of taken blood cultures including its results, the number of taken cultures of suspected sides of infection including its results, antibiotic use including dose, interval and duration of treatment in days, the (suspected) type of infection and relevant laboratory parameters. For the spill over group, we will only collect data concerning the LOS and the possible confounders.

Antibiotics included in the study belong to group J01 (antimicrobials for systemic use) of the Anatomic Therapeutic Chemical (ATC) classification system. When multiple antibiotics are prescribed to one patient, all antibiotics will be registered. Antiviral therapy, medication for tuberculosis, antibiotics used for non-systemic selective intestinal decontamination and antibiotics used as pro-kinetics will be excluded.

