### Sample size

The power analysis is based on previous results of appropriate antibiotic use on length of stay as described at ‘background’ [6,7]. In a simulation study based on the stepped wedge design, with nine hospitals each contributing 180 patients with a suspected infection, we estimated the power to approximate 80% to demonstrate a significant reduction of 13% in length of stay, assuming that the intraclass correlation coefficient does not exceed 0.20. With each hospital contributing 180 patients with a suspected infection, the total sample size will be 1620 patients. For each hospital we have determined a minimum number of patients in the baseline group and intervention group, depending on the randomization order of the hospital in the stepped wedge.

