### Analysis

#### Effect evaluation

We will use mixed linear models to analyse the overall effect of the introduction of the checklist on length of stay. Therefore we will evaluate differences between baseline (before introduction of the checklist) and intervention plus spill over (after introduction of the checklist) (intention to treat analysis). We will also determine the theoretical effect of the checklist on LOS by evaluating differences between baseline and intervention data without the spill over data (per protocol analysis). Differences between the baseline data and the intervention data for secondary outcomes will also be evaluated with mixed linear models. For dichotomous outcomes (mortality), the comparison will be evaluated with a similar approach, using generalized estimating equation models. These mixed models account for within-cluster dependencies, and allow adjustment for possible confounders. To assess whether differences between these groups may be explained by confounding patient characteristics, we will first test with multivariate multilevel (linear mixed) analyses if these variables have a significant effect (p < 0.05) on the outcomes. Hereafter, we will compute the estimate of the total causal effect of checklist implementation on the outcomes before and after adjusting for a significant variable. If the estimate varies 10% or more, possible confounding is present and in that case we will adjust for this variable.

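### The screening rule for confounders (p < 0.05, then a 10% change taken one variable at a time) makes the adjustment set depend on the observed effect, can leave joint confounding in place and loses some precision

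*Protocol article*

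**What the plan says.** The protocol's Assessments section lists the possible confounders: "namely age, sex, community-or hospital acquired infection, Charlson comorbidity index", followed by antibiotic use in the previous 30 days and the Modified Early Warning System, six in all. They are collected in every group, including the spill-over patients for whom little else is recorded.

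The Effect evaluation section then fixes how they are used. The main tool is stated first: "We will use mixed linear models to analyse the overall effect of the introduction of the checklist on length of stay". For the covariates, "we will first test with multivariate multilevel (linear mixed) analyses if these variables have a significant effect (p < 0.05) on the outcomes". Next, the effect of the checklist is estimated "before and after adjusting for a significant variable". Finally: "If the estimate varies 10% or more, possible confounding is present and in that case we will adjust for this variable".

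The same paragraph sets up two length-of-stay comparisons: an intention-to-treat contrast of baseline with everyone after introduction, and one "evaluating differences between baseline and intervention data without the spill over data (per protocol analysis").

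**The concern.** This is a stated algorithm, so it is not a detail left to an analysis plan. Three features of it are weak.

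- **The threshold moves with the result.** Ten percent of a small estimate is tiny, so chance imbalance triggers adjustment. Ten percent of a large estimate is wide enough for real confounding to pass.
- **The 10% step looks at one variable at a time.** The significance screen is multivariate, but the change in estimate is judged for a single variable, with no joint check. Several modest confounders acting in the same direction can each pass below the threshold.
- **Prognostic value alone earns nothing.** A variable that strongly predicts length of stay but happens to be balanced is dropped, although including it would reduce the standard error.

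At stake are the length-of-stay estimates. The per-protocol comparison is the most exposed: whether a checklist is completed is not randomised, so that contrast relies on covariate adjustment.

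**Working it through.** **Inputs from the protocol.** Nine hospitals with 180 patients each; a power of about 80% "to demonstrate a significant reduction of 13% in length of stay"; intraclass correlation up to 0.20; introduction over four time periods; six candidate covariates; thresholds p < 0.05 and 10%.

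**Assumptions.** Analysis of log length of stay; two-sided 5% test; 2, 2, 2 and 3 hospitals crossing over at four steps in five periods (the layout figure is not shown); hospital fixed effects in place of a random intercept; six equal, independent covariates jointly explaining a share R² of within-hospital variance. Models were run with and without period effects, with residual SD 0.55 and 0.88 respectively, chosen so that unadjusted power is 80%. Each setting used 2,000 to 8,000 simulated trials.

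**The plan's own figures.** 9 × 180 = 2 × 810 = 1,620, as stated. The 80% power can be neither confirmed nor refuted, because no SD is given. At an intraclass correlation of 0.20 it needs a total log-SD of about 0.59–0.62 with period effects, or 0.99–1.02 without.

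**1. Dependence on the effect.** A 13% reduction is ln(0.87) = −0.139 on the log scale. The threshold there is 0.10 × 0.139 = 0.014, against a standard error of about 0.05. As the estimate approaches zero, so does the threshold. With R² 0.20 and no confounding:

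| True effect | Mean covariates kept (of 6) | Trials keeping none |
|---|---|---|
| Null | 4.1 | 2% |
| 13% reduction | 1.0–1.1 | about 45% |

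The covariates are the same in both rows; only the effect differs.

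**2. Joint confounding.** Let each covariate bias the effect by 7% of its true value in favour of the checklist. The joint bias is 6 × 7% = 42%, and the expected unadjusted estimate is −0.139 × 1.42 = −0.197. Relative to that estimate each single shift is 0.07/1.42 = 4.9%, well under 10%. Simulated means (R² 0.20, period effects): unadjusted −0.199, all six −0.140, rule −0.179. The share of bias left is (0.179 − 0.139)/(0.199 − 0.139) = 0.040/0.060, about two thirds. No covariate is kept in 42% of trials. Over repeated trials the rule's estimate has SD 0.059, while the model reports a standard error of 0.049. With R² 0.05, about 85% of the bias stays.

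If the same six shifts act against the checklist, the unadjusted estimate is −0.139 × 0.58 = −0.081 and each shift is 0.07/0.58 = 12% of it. That exceeds the threshold, so most of the bias is removed.

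Under a true null with the favourable shifts, the mean estimate is −0.058 unadjusted and −0.005 under the rule. False positives are 21.6% unadjusted, about 7.6% under the rule and about 5% with all six.

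**3. Precision.** Without confounding, power with all six is Φ(2.80/√(1 − R²) − 1.96), where 2.80 = 1.96 + 0.84. At R² 0.20: 2.80/0.894 = 3.13, and Φ(1.17) = 88%.

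| R² | Unadjusted | Rule (simulated) | All six (formula) |
|---|---|---|---|
| 0.05 | 80% | 81–82% | 82% |
| 0.10 | 80% | 82% | 84% |
| 0.20 | 80% | 84% | 88% |
| 0.30 | 80% | 87–88% | 92% |

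Simulated power with all six at R² 0.20 is 87–88%. The rule recovers about half of the available gain at R² 0.10 and 0.20.

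**4. Type I error without confounding.** Rejection under the rule is 3.3–5.0%, so there is no inflation.

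**The case against.** The best defence is that the rule is mechanical. The six candidates and both thresholds are fixed in advance, so the analyst has no discretion. Without confounding it does not raise the false-positive rate and never fell below unadjusted power, so the planned power is not damaged. The intention-to-treat contrast follows a randomised order of introduction, and nothing in the protocol shows that six imbalances would line up in one direction. The precision gain rests on an R² that the protocol does not give. All of this stands, and it limits the size of the point. It does not answer the dependence of the model on the result or the missing joint check, and it does not protect the per-protocol comparison.

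A reader might infer more than the document supports:

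- **Six shifts of 9% would all be ignored, leaving 54% of the estimate unadjusted.** This is a constructed worst case. With expected shifts of 9% of the unadjusted estimate, a simulation (SD 0.7, intraclass correlation 0.1, R² 0.20) left all six out in only about 5% of trials. The mean moved from −0.140 unadjusted to −0.088 under the rule, against −0.067 with all six: (0.140 − 0.088)/(0.140 − 0.067), or about 70% of the bias removed.
- **Acquisition type must be in the model.** The different start points for length of stay make it prognostic, but it biases the contrast only if the mix changes after introduction.
- **Estimates in logistic models shift without any confounding.** The protocol names generalized estimating equations for dichotomous outcomes but no link, so this cannot be asserted.
- **Different adjustment sets across outcomes are an error.** They are not one in themselves; outcomes can have different confounders.

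**Conclusion.** The concern holds in a moderate form. The rule ties the adjustment set to the observed effect, can leave several same-direction confounders uncorrected when they favour the checklist, and gives up some precision. Under the stated assumptions with R² 0.20, it keeps about 4 of 6 covariates under the null and about 1 of 6 at a 13% reduction. It leaves about two thirds of a joint bias made of six favourable 7% shifts, and costs 3 to 4 points of power, or about 2 points at R² 0.10.

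The direction of these results follows from the wording of the rule. Their size depends on the assumed R², SD, layout and independence of covariates, none of which the protocol supplies. It would be wrong to conclude that the primary test is invalid or that the trial is underpowered because of this rule.

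**What to change.** Delete the screening rule for both length-of-stay analyses, intention to treat and per protocol. Replace it with a statement that both models adjust for age, sex, community- or hospital-acquired infection, Charlson index, antibiotics in the previous 30 days and early-warning score, whatever their p-values and however much they change the estimate. Report the model without these six as a sensitivity analysis. Acquisition type is a particularly strong candidate, because length of stay runs from admission in one group and from the start of antibiotics in the other.

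For the dichotomous secondary outcomes, also replace the rule with a set named in advance, but make it smaller where events are few. The full six need not be imposed on mortality or ICU admission.

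The cost is a change of wording and a few degrees of freedom in at least 1,620 patients. No new data are needed, since all groups already have the six variables recorded. The one added task is to state how missing covariate values will be handled, because a fixed covariate set would otherwise drop patients with gaps.

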#### Validation and process evaluation

We will evaluate the physicians’ compliance with the checklist. Firstly we will check whether the ticks in the completed checklists are in accordance with the performance in clinical practice. Secondly we will determine the percentage of eligible patients for whom the checklist has been used after checklist introduction. The number of patients in whom the checklist was actually used (the intervention group) will be divided by the number of patients in whom it should have been used (the intervention plus the spill over group).

#### Economic evaluation

The key question for the economic evaluation is whether the benefits of using the checklist, which will likely include reduced antibiotic use, reduced length of stay and associated costs, justify the costs associated with implementation activities as well as daily use of the checklist. For reasons of feasibility, the cost analysis will only include a few main cost drivers of health care utilization, namely LOS on a general or ICU ward and antibiotic use. Unit costs for health care utilization will be estimated according to the Dutch guideline on (unit) costing in health care [18]. LOS and ICU stay will be valued based on the guideline prices. Furthermore, we will compare the total antibiotic use in days per antibiotic class in the baseline and the intervention group. Antibiotic costs will not be valued because the benefits become more evident in terms of reduced quantities rather than their particular costs. Implementation costs will be divided in non-recurring and recurring costs. Non-recurring costs are related to our study, such as costs of the development of the materials, the implementation strategy and costs of evaluation of the implementation. Recurring costs are the costs of accomplishment of the implementation strategy. The primary analysis is a cost-effectiveness analysis, with the incremental cost-effectiveness ratio expressed as the implementation related costs per reduction of length of stay in days. As we hypothesize that an effective implementation of the checklist will result in reduced health care use and thus lower costs, we will also perform a cost-benefit analysis, evaluating whether the implementation costs are offset by this cost reduction (costs of implementation < health care cost reduction). Robustness of the results for uncertainty in the assumptions will be evaluated in sensitivity analyses, including estimates of unit costs and volume of implementation activities (considering less activities will be needed if checklists become part of standard care). In a budget impact analysis results from the economic evaluation will be extrapolated to the national level to estimate the total clinical and budget impact in terms of health benefits, reduction in antibiotic use, and associated economic impact on the health care budget per annum for the Netherlands. The budget impact analysis will be performed according to the criteria provided by Mauskopf et al. [19], from a societal perspective as well as from the health insurance and/or national health care budgeting framework perspective. We will evaluate the impact of varying implementation rates, comparing care as usual (0% implementation), potential impact (100% implementation), and the probable rates of 85% and 50% implementation.

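### The cost-benefit test and the budget impact analysis give no money value to antibiotic use, a listed main cost driver, and the budget impact is called societal without societal costs

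*Protocol article*

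**What the plan says.** All references are to the protocol article. The Economic evaluation section keeps the list of cost drivers short for feasibility, "namely LOS on a general or ICU ward and antibiotic use". It then says which of them get a price: "LOS and ICU stay will be valued based on the guideline prices". Antibiotics are handled differently: "we will compare the total antibiotic use in days per antibiotic class in the baseline and the intervention group", followed by "Antibiotic costs will not be valued because the benefits become more evident in terms of reduced quantities rather than their particular costs".

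The primary economic analysis is a ratio of implementation costs to hospital days saved. A cost-benefit analysis is added, "evaluating whether the implementation costs are offset by this cost reduction (costs of implementation < health care cost reduction". A budget impact analysis then carries the results of the economic evaluation to the national level, "from a societal perspective as well as from the health insurance and/or national health care budgeting framework perspective". Its intended outputs include the reduction in antibiotic use and the resulting effect on the health care budget.

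Under Assessments, the data recorded to compute the quality indicators include "antibiotic use including dose, interval and duration of treatment in days" and the numbers of blood cultures and of cultures from the suspected site. For spill over patients only LOS and the possible confounders are collected.

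**The concern.** A cost-benefit test is a comparison in money, so a resource without a price cannot enter it. The section opens by asking whether benefits that include lower antibiotic use, shorter stay and the related costs justify the cost of implementing and using the checklist. As planned, the money comparison can answer that question for hospital and ICU days only. The reason given for not pricing antibiotics, that quantities show the benefit more clearly, is a good reason to report quantities. It does not justify leaving a listed driver out of a test expressed in money.

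The budget impact analysis inherits the gap. Its effect on the health care budget would exclude drug costs even from the payer's side. Its societal label promises a scope that the listed cost items do not have. Readers who use the national figures could take them to be more complete than they are.

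**Working it through.** The article gives no unit price, implementation cost or cost-effectiveness ratio, so there is no economic figure to reproduce. The check is mainly textual.

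**Step 1: what is listed, what is priced, and where it enters.**

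| Item | Listed as cost driver | Priced | In primary ratio | In cost-benefit test |
|---|---|---|---|---|
| General-ward days | yes | yes | LOS is the effect (denominator) | yes |
| ICU days | yes | yes | no separate term | yes |
| Antibiotic use | yes | no | no | no |
| Cultures | no | no | no | no |
| Implementation | separate cost category | yes | numerator | yes |

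Antibiotic use is the only item that is listed as a driver and not priced. The planned sensitivity analyses on unit costs cannot fill the gap, because antibiotics have no unit cost to vary.

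**Step 2: the test.** Write C for implementation cost per patient, B for the saving on hospital and ICU days, A for the saving on antibiotics (negative if use rises) and K for any added cost of cultures.

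- As planned: C < B.
- With the omitted items: C < B + A − K.

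The two versions disagree only if C lies between B and B + A − K. Omitting a positive A understates the benefit; omitting a positive K overstates it. The documents give none of C, A and K, so neither the sign of A − K nor any change in the answer can be established.

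**Step 3: scale, for illustration only.** Inputs from the Background section: a 13% LOS reduction with appropriate use, and mean stays of 7.3 and 8.7 days from a urinary tract infection study.

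- Days saved: 0.13 × 7.3 = 0.949 and 0.13 × 8.7 = 1.131, so about 0.95 to 1.13 days per patient.
- Let x be the assumed net omitted amount in bed-day equivalents. The relative shift in the valued LOS saving is x / (0.13 × LOS).

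| Assumed x | LOS 7.3 days | LOS 8.7 days |
|---|---|---|
| 0.05 | 0.05/0.949 = 5.3% | 0.05/1.131 = 4.4% |
| 0.10 | 0.10/0.949 = 10.5% | 0.10/1.131 = 8.8% |
| 0.20 | 0.20/0.949 = 21.1% | 0.20/1.131 = 17.7% |

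The shift may go either way. It is inversely proportional to the LOS effect: if the true reduction were half of 13%, each percentage would double. The values of x are assumptions.

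**Step 4: perspective.** The priced items are hospital days, ICU days and implementation. No listed item lies outside hospital care and implementation, so the extrapolated result cannot be broader than that. The societal label is attached to the budget impact analysis only; no perspective is named for the cost-benefit test.

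**Step 5: can the gap be closed with the planned data?** For baseline and intervention patients, yes: antibiotic use and culture counts are recorded. For spill over patients, no. The intention-to-treat comparison defined under Effect evaluation includes spill over patients, so priced antibiotics are available only for the per-protocol comparison.

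**The case against.** The choice is disclosed and reasoned. The short list is explained by feasibility, and antibiotic use is not dropped: it is a secondary endpoint, it is compared in days by class, and its reduction is a named output of the budget impact analysis. Because spill over patients have no antibiotic data, pricing cannot cover the whole post-introduction population. Mixing intention-to-treat LOS savings with per-protocol antibiotic savings would be worse than the present plan. The primary ratio would not change at all.

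Most of this stands and limits the point. It does not remove the inconsistency: reporting in days does not put a listed driver into a money test. The data limit also does not single out antibiotics, since ICU duration is likewise collected only for baseline and intervention patients and is priced nonetheless.

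Three stronger readings are tempting and are not supported:

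- **The omitted items could decide the cost-benefit test.** Without an implementation cost or any price, this cannot be shown.
- **The checklist raises culture costs that the plan ignores.** The checklist contains the seven process indicators, and cultures are counted to compute indicator performance, so a culture item is a reasonable inference. But the figure with the items is not available, and no increase in cultures is stated.
- **The cost-benefit test is presented as societal.** It is not; that label belongs to the budget impact analysis.

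**Conclusion.** The point holds as a limited inconsistency in the secondary economic analyses. Antibiotic use is named as a main cost driver and then left unpriced, so the cost-benefit test and the budget impact analysis built on it count savings on hospital and ICU days only. The budget impact analysis also claims a societal perspective that its cost items do not support. The primary cost-effectiveness ratio, the primary endpoint and the sample size are untouched.

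The size and direction of the omission are unknown. The shift of about 4% to 21% rests on an assumed 0.05 to 0.20 bed-day equivalents per patient, on the planned 13% effect, and on stays of 7.3 to 8.7 days from one type of infection. It shows scale and is not an estimate. This is a minor point, worth correcting because it changes what the economic conclusions may claim.

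**What to change.** 1. Keep hospital and ICU days as the main cost difference, and continue to report antibiotic days by class.
2. Add a sensitivity analysis of the cost-benefit test and the budget impact that prices recorded antibiotic use at list prices for baseline versus intervention patients. Include culture counts if the checklist prompts cultures. Confirm that route of administration is recorded, since the article lists only dose, interval and duration.
3. Label this analysis as the per-protocol comparison. Alternatively, bound the effect for all post-introduction patients by assuming no antibiotic change in the spill over group: with p the share of eligible patients with a completed checklist and a the mean saving among them, the average saving is p × a + (1 − p) × 0 = p × a. This is a lower bound only if antibiotic use did not rise in spill over patients.
4. In the budget impact analysis, replace the societal perspective with the health insurance or health care budget perspective already named there.

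The cost is a price list and a little more analysis, with no new data collection provided route is recorded. The supplementary result is open to selection by checklist completion, and the economic claim becomes narrower.
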